#### PNE program

This modern PNE program is tailored to the pain needs of survivors of cancer, and the educational content is based on the book “Explain Pain” [18], the Pain In Motion website (http://www.paininmotion.be) and ‘The Pain Toolkit’ [27]. Participants will acquire PNE contents at home during the first two weeks [28] of the MR program. PNE sessions will be delivered to the patients through the PaiNEd app, developed by the BIO277, CUIDATE research group. The app will display lessons following this order (Fig 3), lasting 20 minutes each one. Participants will need a mobile device or tablet with an internet connection and Android or iOS operating systems. They will have access to the app to learn and review the educational contents at home on demand (in video and infographic format).

**Fig 3 pone.0290096.g003:**
[figure not shown]
Overview of the PNE program.

#### Multimodal rehabilitation program

The MR program features supervised exercise and manual therapy. It will be fully supervised by a physiotherapist who specializes in the implementation of exercise programs and manual therapy in the oncological population and will be individualized to the needs and circumstances of the participants.

*Exercise*. Patients will receive 3 nonconsecutive sessions per week at the CUIDATE unit, and the program will last 8 weeks. An overview of the exercise program is presented in Table 2. The combined resistance and aerobic exercise program will follow the American College of Sports Medicine (ACSM) exercise guidelines [29]. The first and third sessions of the week will consist of 60 minutes of concurrent exercise [30], and the second session will feature 60 minutes of aerobic exercise.

**Table 2 pone.0290096.t002:** Overview of the exercise program.

Principles		Concurrent exercise	
	Aerobic exercise		Resistance exercise
Frequency	3 sessions/week		2 sessions/week
Intensity	40–60% HRR		50–70% RM [32]
	Borg CR10 RPE: 3–4 [31]		Borg CR10 RPE: 5–7
Time	Session 1 of the week: 30 minutes		Session 1 of the week: 30 minutes
	Session 2 of the week: 60 minutes		Session 3 of the week: 30 minutes
	Session 3 of the week: 30 minutes		
Type	Elliptical cross-trainer exercise		Squats, stiff-legged deadlifts, shoulder press, unilateral rows, reversed flies and push-ups
			Week 1 to 5: 2x12-20 reps
			Week 6 to 8: 3x10-12 reps
Progression	40–50% HRR; Borg CR10 RPE: 3 (weeks 1 to 4)		When a participant can perform 2 sets, in 2 consecutive sessions with appropriate form, the exercise will be progressed through increasing the resistance by the smallest available increment
	50–60% HRR; Borg CR10 RPE: 4 (weeks 5 to 8) [33]		

HRR: Heart rate reserve; RM: Repetition maximum; RPE: Rating of perceived exertion

*Manual therapy*. Participants will receive 1 manual therapy session every 2 weeks. Each session will last approximately 30 minutes. Treatment sessions will be developed based on previously published protocols that demonstrate effectiveness in treating pain and dysfunction in oncology patients [33, 34]. The current protocol will involve manual and myofascial techniques focusing on the cranio-cervical, thorax and shoulder regions, adapted to the patient´s tissue response [35].

#### Outcomes

All participants will receive written and verbal informed consent and a signed copy of the consent form with the Principal Investigator’s contact details if they have more questions, previous to first assessment. Participants are informed that they can leave the study at any time without penalty or loss of benefits. Eligible participants will not suffer any potential harm in the study. There are no economic incentives for participating in the study. If significant changes regarding objectives, eligibility criteria, outcomes or interventions occur, a formal amendment to the protocol will be needed. Therefore, approval by the Ethics Committee of the Junta de Andalucía and the research team will be required. Clinical data will be taken from the electronic medical records by the participating health personnel. A questionnaire based on sociodemographic issues will be provided at the beginning of the assessment. Questionnaires are collected through the PaiNEd app.

#### Primary outcome (Perceived pain)

The visual analog scale (VAS), offers a subjective pain estimation. The VAS is a 100 mm straight line starting with 0 that represents “no pain” and ends with 100 representing “worst pain imaginable” [36]. The VAS has been used in multiple situations and has proven to be a reliable and appropriate tool to measure pain [36].

#### Secondary outcomes

*Pain catastrophizing*. The Pain Catastrophizing Scale (PCS) is a self-administered scale of 13 items and one of the most used tools to assess catastrophizing in the face of pain. Patients take as a reference their past painful experiences and indicate the level to which they experienced each of the 13 thoughts or feelings in a Likert scale of 5 points that goes from 0 (never) to 4 (always). A total score is obtained from the scale that reflects the level of catastrophizing in the face of the patient’s pain. It contains 3 aspects: a) rumination (constant worry and inability to inhibit thoughts related to pain); b) magnification (the exaggeration of the unpleasantness of situations of pain and expectations of negative consequences), and c) helplessness (the inability to face painful situations). The values of the instrument range between 13 and 62, indicating low scores, low catastrophizing, and high values, high catastrophizing [37]. The PCS has proven to be reliable for daily use in participants reporting chronic pain [37].

*Central sensitization*. The Central Sensitization Inventory (CSI) is composed of two different parts. The first one consists of 25 statements, each answer is scored: 0 Never, 1 Rarely, 2 Sometimes, 3 Often, and 4 Always. So that, at most we will be able to obtain a score of 100 and a minimum of 0. The second part is a survey in which patients explain if they have been diagnosed of specific disorders. Higher CSI scores mean greater symptoms of CS. If patients obtain a score greater than or equal to 40, we will consider that they have sufficient psychometrics to be correlated with CS syndromes [38]. The CSI has shown to be a valid and reliable measure for detecting CS symptoms in survivors of BC [38].

*Kinesiophobia*. Kinesiophobia will be measured by an 11-item version of the Tampa Scale of Kinesiophobia (TSK-11). Each item has 4 response options, “strongly disagree” scores 1 point, and “strongly agree” scores 4 points. The maximum possible score is 44 points and the minimum is 11 points. Greater scores mean strong fear of movement. The Spanish version showed good reliability and validity [39].

*Quality of life*. The European Organization for Research and Treatment of Cancer (EORTC). Created a general quality of life questionnaire known as EORTC–C30 [40]. It is a multidimensional, self-administered questionnaire that consists of 30 questions (Likert type) that is used for all cancer patients (qlq-c30). Global quality of life, functionality (physical, role, emotional, cognitive, and social functioning) and symptomatology (fatigue, nausea and vomiting, pain, dyspnea, insomnia, appetite loss, constipation, diarrhea, and financial difficulties) are evaluated [41]. When analyzing the EORTC questionnaires, scores are obtained in a range from 0 to 100. On the functional items, a higher score means better functioning, and on the symptom items, a higher score turns into a greater presence of the adverse effects. The EORTC QLQ-C30 had an adequate test–retest reliability with an ICC ranging from 0.698 to 0.926 in cancer survivor patients [41].

The QLQ BR-23 module for BC [42], consist of 23 questions covering symptoms and secondary effects related to the different treatment modalities; also includes aspects such as body image, sexuality and future prospects [43]. The BR-23 module has a Cronbach’s α coefficient of 0.873 [44].

*Level of physical activity*. The International Physical Activity Questionnaire (IPAQ) is one of the most used generic physical activity (PA) questionnaires [45]. The short form of IPAQ (IPAQ-SF) consists of 7 questions about the frequency, duration and intensity of PA (vigorous and moderate) performed the last 7 days, as well as walking and sitting time on a working day. Weekly PA is obtained with the calculated MET-minutes within each PA intensity level MET score (Walking  =  3.3 METs, Moderate Physical Activity  =  4.0 METs and Vigorous Physical Activity  =  8.0 METs) [46]. The PA level is classified as ‘high’ (>1500 METs), ‘moderate’ (600–1500 METs), or ‘low’ (<600 METs). The IPAQ-SF has demonstrated acceptable validity in an adult Spanish population [47]. ICC = 0.64; (0.55–0.72) [48].

*Active Range of Motion (AROM)*. A plastic universal goniometer with two adjustable overlapping arms is used to objectively measure the active range of motion of the shoulder joint with the patient placed in the supine position [49]. A cervical range of motion device (Performance Attainment Associates©, Spine Products, Roseville, MN, USA) is used to objectively measure the active range of motion of the cervical joints (sitting position and feet completely in contact with the floor) [50]. AROM measurements are bilaterally performed three times, and the average values are used for the study. Reliability of shoulder AROM was high in survivors of BC, with ICC values ranging from 0.66–0.97. [51]. Cervical AROM is reliable and valid for evaluating the cervical AROM (ICC range: 0.82–0.96) in patients with neck pain [52].

*Functional capacity*. The Six-Minute Walk Test (6MWT) determines the maximum distance (meters) that a person can walk in 6 minutes. The test take place in a 30-metre stretch of unimpeded walkway. Blood pressure, blood oxygen saturation and Borg’s modified Scale (0–10) of RPE are provided at the beginning and the end of the test. Heart rate is measured during the test. Patients are notified when each minute passes and standardized encouragement is given during the test [53]. The test has proven to be reliable as it obtained an ICC of 0.93 in cancer patients [54]. Minimal important difference was established between 22 m (95% CI 18–26) and 32 m (95% CI 20–42) [55].

*Hand-grip strength*. Grip strength is assessed with a manual dynamometer (TKK 5101 Grip-D; Takey, Tokyo, Japan) [56]. The test can be done with the patient in standing position. The elbow is fully extended, the forearm neutral for pronosupination and wrist extension between 0 and 30°. Patients are asked to squeeze the dynamometer as hard as possible. Phrases of encouragement are given to patients in order to achieve their maximum force. The test is repeated three times bilaterally to obtain the mean of each grip. ICC scores range from 0.88 to 0.96 demonstrating high reliability in survivors of HNC [57].

*Deep Neck Flexor (DNF) endurance*. The DNF endurance test measures the endurance of the deep flexor muscles of the neck [58]. It consists of placing the patient in supine position with the spine fully supported on the stretcher and asking him to first, to do a flexion of the upper cervical spine and to simultaneously flex the lower cervical spine. The time that the patient is able to maintain the position without losing the initial distance that separated him from the stretcher is counted. The test will stop if the participant reports pain or if he can no longer maintain the position. Reliability of DNF endurance test was moderate as ICC = 0.66 [59].

*Body composition*. Direct Segmental Multi-frequency Bioelectrical Impedance Analysis (DSM-BIA) is used for assessing skeletal muscle mass (Kg), fat mass (%) and body weight (kg). DSM-BIA is evaluated using the In-Body 720 body composition analyzer (Biospace, Seoul, Korea), following the instructions of the user’s manual [60]. Patients will be told not to eat or drink one hour before the test. BIA appeared to have very high reliability at estimating body fat percentage in survivors of BC as ICC = 1 [61] and 0.95 at estimating muscle mass in women [62].

### Inflammatory and stress response

Saliva will be collected in the morning period (09:00 to 11:30 a.m.) [63]. The salivary biomarkers Cortisol and Interleukin 6 (IL6) will be measured with a commercial luminescence immune assay (Salimetrics, State College, PA) and the Salimetrics IL-6 ELISA Kit respectively. Cortisol is modulated by chronic stress generated by the constant pain endured by the patients [64]. IL6 is the cytokine which regulates inflammatory response to physical or psychological (affective) alteration of the organism. Some precautions must be taken for its collection, as participants will be instructed to not brush their teeth for at least 30 minutes before and to avoid eating, drinking and performing PA at least 3 hours before.

### Data collection and security

To enhance the retention of treatment groups, the app will show users when they come to the cancer rehabilitation research unit for assessments or multimodal treatment sessions, as well as how many weeks and sessions remain. Participants will also be notified of their assessment and treatment appointments by phone or e-mail according to their preferences.

The mobile app will be installed in each patient’s mobile and instructions about how properly use it will be given. All data will be stored in accordance with the European General Data Protection Regulation.

Only the researchers involved in the PaiNEd protocol will have physical access to all pseudoanonymized and encrypted information, with the server located at the University of Granada (Granada, Spain). This will ensure the safety of data management. Personal data will be handled in a way that they can no longer be attributed to study participants, following the principles of anonymity and confidentiality throughout the study.

### Data analysis

To analyze the results, the statistical program IBM SPSS 26 (IBM Corp., Armonk, NY, USA.) will be used. The descriptive statistics for this study (95% confidence intervals) will use mean and standard deviation (continuous data) or frequencies and percentages (categorical data). The Kolmogorov-Smirnov test will be applied to verify the normal distribution of the variables (p> 0.05). Receiver operating characteristic (ROC) curves will be included to determine the accuracy of the tests. A t test will be used to analyze parametric variables, and a Mann–Whitney U test will be used for nonparametric variables. From the point of view of inferential statistics and to respond to the main objective of this study, an intention-to-treat analysis will be carried out. A 3x3 repeated-measures ANOVA model will be performed using time (baseline, postintervention, follow-up) as a within-subject factor and intervention (first arm, second arm, control) as a between-subjects factor. The Bonferroni test will be used for post hoc analysis. For the study on subgroups with possible differential results, cancer location, type of treatment, elevated tumor stages, age, sex will be used as possible confounding variables in a subsequent multiple regression analysis. A significance level of p value less than 0.05 (P < .05) will be considered. The intergroup effect sizes will be calculated to provide magnitude changes; the effect size will be estimated using Cohen’s d (0–0.19, negligible; 0.20–0.49, small; 0.50–0.79, moderate; ≥0.8, large).

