### Calculation of the sample size

The estimation of the sample size and statistical power for the trial were determined based on the main variable, pain measured through the VAS. Based on a previous study [26] and estimating that patients in the intervention group would have a difference of 15 mm or more in the VAS compared to the control group, differences of at least 5% can be detected with a statistical power of 90% and a significance level alpha α of 0.05. This will require a sample of 24 patients per group, which will result in a total of 72 participants. Therefore, a maximum monitoring loss of 20% will be allowed. To carry out this sample calculation, the G*Power v. 3.1 Software was used.

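### The repeated-measures ANOVA fixed for the main objective uses only participants with all three visits, so without a stated imputation step it does not deliver the promised intention-to-treat analysis

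*Protocol article*

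**What the plan says.** In the protocol article, Data analysis, the plan says that "to respond to the main objective of this study, an intention-to-treat analysis will be carried out". The model follows at once: "A 3x3 repeated-measures ANOVA model will be performed using time (baseline, postintervention, follow-up) as a within-subject factor", with the three arms as the between-subjects factor. On software, "the statistical program IBM SPSS 26 (IBM Corp., Armonk, NY, USA.) will be used". No other model for comparing the arms over time is named, and the article gives no rule for a missing visit: no imputation, no mixed model, no likelihood-based method.

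Loss is foreseen under Calculation of the sample size. There "This will require a sample of 24 patients per group, which will result in a total of 72 participants", and "a maximum monitoring loss of 20% will be allowed". Under Design, the last assessment comes 6 months after the 8-week intervention ends, so missing final visits are to be expected.

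**The concern.** A classical repeated-measures ANOVA (GLM Repeated Measures in SPSS) works on complete rows. A participant with VAS at baseline (t0) and at the end of the intervention (t1), but not at 6 months (t2), leaves the whole analysis, including the t1 comparison to which that participant could have contributed. The named model therefore returns a completers result unless something is added to it, while the sentence beside it promises an analysis of everyone randomised.

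Two things are at stake. One is precision, because observed data are thrown away. The other is bias, if those who leave differ from those who stay in a way that varies by arm. The arms do differ in burden: two attend three supervised sessions a week for 8 weeks (24 sessions), and the third receives a leaflet. The Discussion itself expects that adherence to exercise might be low.

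**Working it through.** **Inputs from the article.** 24 per arm and 72 in total; 20% loss; a 15 mm VAS difference; 90% power and alpha 0.05; visits t0, t1 and t2. **Assumptions.** The test is taken as two-sided. The article gives no SD, so it is back-solved below. Correlations and dropout mechanisms are also assumed.

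**1. Size of the analysis set.** 72 × (1 − 0.20) = 57.6, so about 58 participants; per arm 24 × 0.80 = 19.2, about 19. About 72 × 0.20 = 14.4 participants are excluded. Observed t1 values discarded with them:
- all loss after t1: about 14
- half before and half after t1: about 7
- all loss before t1: none

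**2. The plan's own sample size.** Without an SD, 24 per arm can be neither confirmed nor refuted. Two readings both give 24. Power is from a two-sample t-test with 2n − 2 degrees of freedom and noncentrality (15/SD) × √(n/2).

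| Reading | SD giving 90% power | Power at 24 per arm | Power at 19 per arm |
|---|---|---|---|
| 24 is the number analysed | 15.7 mm (d = 15/15.7 = 0.956) | 90% | 82% |
| 24 includes the loss, 19/(1 − 0.20) = 23.75, rounded up to 24 | 13.9 mm (d = 1.08) | 96% | 90% |

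At any fixed SD, the confidence interval at 19 per arm is wider than at 24 by √(24/19) = 1.12, about 12%.

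**3. Bias from analysing completers.** Simulation with 400,000 per arm, SD 15.7 mm, correlations t0–t1 0.5, t1–t2 0.6 and t0–t2 0.5, and a true difference of 15 mm at both visits. Overall 20% are lost between t1 and t2, with log-odds of loss moving by 0.06 per mm of t1 pain where loss depends on pain (odds ratio exp(0.06 × 15.7), about 2.6 per SD). The table shows the completers' difference in change from baseline.

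| Loss mechanism | t1 contrast (mm) | t2 contrast (mm) |
|---|---|---|
| Same pain-dependence, 20% lost in each arm | 15.0 | 15.0 |
| One common rule, so loss is unequal (about 14% and 26%) | 14.3 | 14.8 |
| Pain-dependent in the intervention arm only, random in the other | 16.3 | 15.3 |
| Opposite directions by arm | 12.4 or 17.6 | 14.5 or 15.5 |

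The pattern follows from the correlations. If selection shifts mean t1 pain by s mm more in one arm than in the other, the t1 change contrast moves by (1 − 0.5) × s and the t2 change contrast by (0.6 − 0.5) × s. With s about 5 mm, that is 2.5 mm and 0.5 mm.

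The small t2 figure therefore depends on the assumed mechanism. In a separate, harsher illustration (SD 15.7 mm, all correlations 0.5, no true effect), one arm lost exactly the 20% with the least improvement at t1 and the other lost 20% at random. The completers' t2 contrast was then off by 2.7 mm. An estimate using all observed t0 and t1 values under missing at random was off by about 0.1 mm.

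**The case against.** The strongest reply is that the article never says completers only. Missing-data rules are commonly left to a full protocol or analysis plan, and imputing before the ANOVA, which SPSS allows, would restore all 72. That stands in part. A reader might infer that the intention-to-treat sentence and the ANOVA cannot both hold. The article does not support that, because imputation would reconcile them. But the point is not mere silence: the article has chosen the model, that choice causes the exclusion, and nothing in the text offsets it.

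A reader might also infer that power certainly drops to 82%. It does so only if 24 is the number analysed. The sample size section does not say whether the 20% is already inside the 24, and on the other reading there is no shortfall.

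Nor do the documents support reading 12.4 or 17.6 mm as the expected result. Those figures need dropout that depends on pain in opposite directions by arm, for which the article gives no evidence. It describes retention measures (visit information in the app, phone or e-mail reminders) and offers controls the multimodal programme after their measurements, which is a reason to stay. The 20% is a ceiling, not a forecast. Loss that differs by arm is plausible given the unequal burden, but it is not established.

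**Conclusion.** The concern holds in a limited form. As written, the model for the main objective would analyse about 58 of 72 participants at the allowed loss and would discard t1 scores already in hand, beside a sentence that promises intention-to-treat. This rests on two things only: the named ANOVA needs complete rows, and no imputation is stated.

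The effect on the results is conditional. Power is about 82% or about 90%, depending on what 24 per arm means. Bias at t1 is nil with the same mechanism and equal loss in each arm, about 1.3 mm with pain-dependent loss in one arm only, and about 2.5 mm in either direction with opposite mechanisms, against a 15 mm target. At t2 it is about 0.5 mm or less under the same correlations and dropout on t1 pain, and larger under the harsher selection shown above. Severity: should-fix.

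**What to change.** Replace the repeated-measures ANOVA with a likelihood-based linear mixed model (SPSS MIXED) on all observed VAS values, with arm, time, arm × time, baseline adjustment and an unstructured covariance. Report the arm contrasts at t1 and at t2.

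State how participants with no post-baseline VAS stay in the intention-to-treat set, since a model with baseline only as a covariate would leave them out. Either model t0 as an outcome with a baseline mean common to the arms, or use multiple imputation. If the ANOVA is to be kept, multiple imputation before it would also meet the point. Add a delta-adjusted sensitivity analysis, because both approaches assume data missing at random. One sentence saying whether 24 per arm includes the 20% would settle the power question.

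The cost is analysis wording in the same software, with no new data, visits or participants. It is most credible if fixed before unblinding.

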**Fig 2 pone.0290096.g002:**
[figure not shown]
Overview of the study.

The inclusion and exclusion criteria for eligible participants of the study are detailed in Table 1.

**Table 1 pone.0290096.t001:** Inclusion/Exclusion criteria.

Inclusion criteria	Exclusion criteria
a) Survivors of BC cancer [25]	a) Physical or mental impossibility of carrying out the tests of the study
b) Aged 18 years or older	b) Have suffered chronic pain in the orofacial, cranial, cervical, brachial and shoulder areas or trauma to these regions prior to the cancer diagnosis
c) Have undergone surgery and/or have finished adjuvant treatment (radiotherapy and/or chemotherapy) at least 6 months up to 2 years ago	c)Participating in other physical recovery programs during the interventions
d) Have no active cancer	
d) Have pain ≥ 4 (VAS 0 to 10) in regions related to the tumor area (orofacial, cranial, cervical, brachial and shoulder) for more than 3 months. e) Pain can be compatible with one or more of these conditions: central sensitization, neuropathy, peripheral pain and pain from surgery	

BC = Breast cancer; VAS = Visual analogue scale.

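### Baseline VAS is an outcome level in the repeated-measures ANOVA and never a covariate, which costs power, and a normality test routes variables to two-sample tests in a three-arm trial

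*Protocol article*

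**What the plan says.** The Data analysis section ties intention-to-treat and a 3x3 repeated-measures ANOVA to the main objective. Time has three levels (baseline, post-intervention, follow-up) "as a within-subject factor and intervention (first arm, second arm, control) as a between-subjects factor". Post hoc comparisons use Bonferroni. The text does not say whether the group effect or the group-by-time interaction is the test. A later regression lists cancer location, treatment, stage, age and sex as covariates; baseline VAS is not among them.

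Earlier in the same section, "The Kolmogorov-Smirnov test will be applied to verify the normal distribution of the variables". Then "A t test will be used to analyze parametric variables", with Mann-Whitney U for the nonparametric ones. No arm pair, visit or outcome is named for these tests.

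Under Primary outcome, "The VAS is a 100 mm straight line starting with 0 that represents “no pain” and ends with 100". The sample-size section assumes that intervention patients "would have a difference of 15 mm or more in the VAS compared to the control group", "with a statistical power of 90% and a significance level alpha α of 0.05", giving 24 per group. Table 1 sets the entry rule: "Have pain ≥ 4 (VAS 0 to 10) in regions related to the tumor area".

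**The concern.** Baseline is measured before treatment, so the arms are equal there in expectation. As an outcome level it can enter a treatment comparison in two ways. It can be subtracted in full, as in a change or interaction contrast, which adds noise unless baseline and follow-up are highly correlated. Or it can be averaged in, as in the group main effect, which shrinks the treatment difference. Using it as a covariate gives it the weight the data support. With 24 patients per arm, the power given up matters.

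The normality rule is a separate weakness of the same section. Two-sample tests do not match a three-arm design. A pre-test on the variables would also let a p-value decide what is reported: Mann-Whitney does not estimate the mean difference in millimetres on which the trial was sized. As written, the rule could apply to VAS and to every continuous secondary outcome.

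**Working it through.** **Inputs.** From the protocol: difference 15 mm, 24 per arm, three arms, alpha 0.05, power 90%, visits t0, t1 and t2. Not in the protocol, so assumed: the SD of VAS, the correlation ρ between visits (taken as equal for all pairs, range 0.3 to 0.7), equal SD at each visit, and two-sided testing.

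**Step 1: the plan's own figure.** For two means, n = 2(1.960 + 1.282)² SD² / 15². With SD 16 mm this is 2 × 10.51 × 256 / 225 = 23.9, so 24. With the exact t test, 24 per group gives 90% power at an SD of about 15.7 mm (15/15.7 ≈ 0.956). The stated 24 is therefore attainable but cannot be verified. One-sided testing would imply about 17.5 mm. If the 24 already contains 20% loss (19 evaluable), it would imply about 14 mm. I use 15.7 mm.

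**Step 2: variance of each arm comparison.** SE = SD × √(2f/24), where f depends on the analysis:

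- t1 only, no baseline: f = 1
- change from baseline to t1: f = 2(1 − ρ)
- ANCOVA at t1: f = 1 − ρ²
- group main effect, mean of three visits: f = (1 + 2ρ)/3, and the effect becomes (0 + 15 + 15)/3 = 10 mm

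The ANCOVA variance is (1 − ρ²)/[2(1 − ρ)] = (1 + ρ)/2 of the change-score variance: 0.65, 0.75 and 0.85 at ρ = 0.3, 0.5 and 0.7. It is smaller at every ρ below 1.

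**Step 3: power.** Pairwise alpha is 0.05/3 = 0.0167. Power comes from the noncentral t with 72 − 3 = 69 error degrees of freedom (one fewer for ANCOVA, which is immaterial).

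| ρ | Change to t1: f, SE (mm), power | ANCOVA at t1: f, SE (mm), power | Main effect, 10 mm: f, SE (mm), power |
|---|---|---|---|
| 0.3 | 1.40, 5.36, 64% | 0.91, 4.32, 84% | 0.53, 3.31, 71% |
| 0.5 | 1.00, 4.53, 80% | 0.75, 3.92, 91% | 0.67, 3.70, 60% |
| 0.7 | 0.60, 3.51, 96% | 0.51, 3.24, 98% | 0.80, 4.05, 51% |

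The t1-only comparison has f = 1, SE 4.53 mm and power 80% at any ρ. Below ρ = 0.5 the change contrast does worse than ignoring baseline altogether.

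**Step 4: the same visits on both sides.** The main effect uses three visits and ANCOVA at t1 uses one follow-up visit. A fairer comparison sets the mean of t1 and t2 minus baseline, f = (1 + ρ)/2 + 1 − 2ρ, against ANCOVA on the mean of t1 and t2, f = (1 + ρ)/2 − ρ². At ρ = 0.5 these are 0.75 and 0.50, giving 91% and 99%. ANCOVA is still ahead, by less.

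**Step 5: the omnibus interaction.** This was simulated with three arms, reductions of 15/7.5/0 mm at both follow-ups, SD 15.7 and alpha 0.05, at ρ = 0.3/0.5/0.7. The group-by-time interaction has power 0.72/0.87/0.98, and omnibus ANCOVA at t1 has 0.86/0.93/0.99. Under the null, the ANOVA tests rejected in about 5% of runs.

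**The case against.** Repeated-measures ANOVA is a legitimate analysis of a randomised trial. It keeps its type I error, and its interaction contrasts do remove chance baseline imbalance, though not efficiently. Whether the arms change differently over time is also, in omnibus form, the short- and long-term question the protocol asks. All of this stands: the fault is lost efficiency, not bias.

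A reader might infer that the trial's planned power is only about 60%. That holds only if the three-visit group main effect is the deciding test, and the protocol does not say so. Read through the interaction, the omnibus loss is about 14, 6 and 1 percentage points at ρ = 0.3, 0.5 and 0.7.

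A reader might also infer that unadjusted t or Mann-Whitney tests across three arm pairs will inflate the family-wise error, to about 11.5% at one visit and about 20% over two. The protocol describes no such procedure, and it links the ANOVA, not these tests, to the main objective. For VAS, the idea of two competing primary answers is therefore weak. What remains is a poor stated rule whose scope is left open.

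Finally, the entry rule truncates baseline, which lowers its correlation with follow-up and so the gain from adjustment. In a two-arm simulation with population SD 20 mm, ρ = 0.5 and alpha 0.05, the observed correlation fell to about 0.35. Power was 83% for ANCOVA, 79% for the t1 t test and 78% for change: a gain of 4 to 5 points.

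**Conclusion.** The point holds as an efficiency and specification fault. ANCOVA beats the t1 change contrast at every correlation tried: by about 20 points at ρ = 0.3, 11 at 0.5 and 2 at 0.7, at the Bonferroni pairwise level. The group main effect, if used, would lose 13, 31 and 47 points to ANCOVA at t1. The direction follows from algebra. The size rests on an SD back-solved from the plan's own sample size and on assumed correlations, neither of which the protocol states, and truncation at entry would make the gain smaller. The normality-gated two-sample rule does not fit a three-arm trial and should not govern between-arm comparisons, but the text does not show that it would override the ANOVA for VAS.

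**What to change.** Analyse VAS with t1 and t2 as the only outcome visits and baseline VAS as covariate, by ANCOVA or a mixed model, with Bonferroni-adjusted pairwise arm contrasts at each visit. Use the same model for each continuous secondary outcome, with that outcome's own baseline. Remove the Kolmogorov-Smirnov gate and the t test/Mann-Whitney rule for between-arm comparisons; check model residuals instead, and keep a rank-based or bootstrap analysis as sensitivity only. Baseline is already collected, so the cost is a change of analysis wording, with no added patients, visits or data.
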